## Abstract

**Background:**

The Achilles tendon is the largest and strongest tendon in the human body. Achilles tendinopathy (AT) is a common clinical problem with Achilles overuse. Eccentric exercise is often used as an initial treatment for these patients. Most patients with AT experienced moderate to severe pain, limiting the incentive to perform eccentric exercise. It is difficult for them to complete eccentric exercise for 3 months consecutively to obtain significant improvements. Using PEMF as an adjunct, there could be immediate pain relief and improved response to eccentric exercise by modulating the mechanical properties of the Achilles tendon. Participants may experience less pain while performing eccentric exercises to increase compliance with the rehabilitation programme.

**Methods:**

This prospective randomised double-blinded, placebo-controlled trial aims to investigate the treatment effects of PEMF for participants with AT. All participants are randomised into two groups: the intervention group (*n* = 20; active PEMF treatment and eccentric exercise) and the control group (*n* = 20; sham treatment and eccentric exercise). Researchers perform self-reported, functional and ultrasonographic outcomes during baseline assessment, 4 weeks, 8 weeks follow-ups, and 3 and 6 months follow-ups after the commencement of the PEMF treatment.

**Discussion:**

AT is a common clinical condition affecting athletes and sedentary populations. It is essential to investigate treatment adjuncts to improve rehabilitation outcomes for these patients. This trial may demonstrate the effectiveness of PEMF in relieving pain, improving function, and restoring mechanical changes of the tendon in participants with AT.

**Trial registration:**

ClinicalTrials.gov NCT05316961. Registered on 7th April 2022.

## Introduction

### Background and rationale {6a}

The Achilles tendon is the largest and strongest tendon in the human body. Achilles tendinopathy (AT) is a common clinical problem with Achilles overuse; it is a clinical condition characterised by a combination of pain and swelling in the posterior leg and heel region. AT results from an altered tendon structure and mechanical properties. It impairs lower extremity function during activities of daily living and athletic capability [1]. A comprehensive treatment plan could optimise the recovery of tendon health and minimise repeated injury risk [2]. There are many limitations in the existing treatments (such as compliance problems in eccentric muscle exercises etc.), with many patients requiring major surgery, such as tendon transfers, due to poor functional improvement after conservative treatments.

The number of Achilles tendon problems has risen in industrialised countries over the past decades [1]. AT is common in athletes who participate in running and jumping sports, with a reported prevalence of 43% in elite track and field athletes and as high as 83% in middle-distance runners [3]. However, it is not purely an athletic injury, with around 65% of injuries unrelated to sports [4].

AT is treated by various interventions, including exercises, orthotics, laser therapy, manual soft-tissue mobilisation, extracorporeal shockwave therapy, injection therapies, surgical debridement, and tendon reconstruction. The treatment with the highest level of evidence is exercise rehabilitation. The exercise aims to provide a mechanical load to the tendon to promote remodelling, decrease pain, and improve calf muscle strength and lower leg function. The loading programmes have consisted of eccentric exercise, isolated concentric, or a combination of concentric and eccentric exercises. They have good reported results in controlled settings, but the effects are limited by poor compliance [2]. Most participants with AT experienced moderate to severe pain, reducing the incentive to perform eccentric exercise. It was difficult for patients to complete the training for 3 months consecutively to obtain significant improvements. Using PEMF as an adjunct, there could be immediate pain relief and improved response to eccentric exercise by modulating the mechanical properties of the Achilles tendon. Patients may experience less pain while performing eccentric exercises to increase compliance with the rehabilitation programme.

Denaro et al. investigated the effects of pulsed electromagnetic fields on human tenocyte cultures. They assessed whether pulsed electromagnetic field therapy (PEMF) could represent a viable therapeutic option in tendon pathologies. A controlled laboratory study evaluated the effects of PEMF on an in vitro tenocyte ‘‘wound’’ closure model. Primary human tenocytes were isolated from healthy supraspinatus and quadriceps tendons. An in vitro cut was mechanically produced in tenocyte culture to mimic the failed healing response in tendinopathy. Compared with the control group, a significant decrease in the ‘‘wound’’ width was found after 12 and 24 h of PEMF exposure. Exposure to PEMF significantly accelerated cut closure 12 and 24 h after the injury. The results supported that PEMF could be a healing-promoting agent in tendon injury. This kind of exogenous stimuli could accelerate the intrinsic tendon healing process by acting directly on tenocytes, the basic cellular component of the tendon tissue, and synthesise collagen and all components of the extracellular matrix. These results provide the preliminary in vitro work and the basis to support the study of the in vivo effects of PEMF on tendinopathies [5].

In addition, a parallel prospective study showed PEMF to reduce pain in patients with AT. Visual analogue scores for pain measurement decreased from 6.9 ± 1.3 at baseline to 3.6 ± 2.0 within 12 weeks [6]. However, there were some limitations in this published study. This study only measured the immediate effect of PEMF on pain in participants. There were no measurements on the functional and mechanical properties of the Achilles tendon, so no evidence supported the long-term impact in this area.

## Objectives {7}

This study aims to investigate the clinical effectiveness of PEMF as a treatment adjunct to eccentric exercise in patients with AT. The objective is to establish whether PEMF plus eccentric exercise in people with AT will improve rehabilitation outcomes compared to eccentric exercise only. The second objective is to investigate the effects of PEMF on pain, functional outcomes, and mechanical and morphological properties of tendons among patients with AT.

## Trial design {8}

This is a prospective randomised, double-blinded, placebo-controlled superiority trial with two parallel groups and a 1:1 allocation ratio to investigate the treatment effects of PEMF for participants with AT. All participants will be randomised into two groups: the intervention group (*n* = 20; active PEMF and eccentric exercise) and the control group (*n* = 20; sham PEMF and eccentric exercise). Researchers will perform all self-reported, functional, and ultrasonographic outcomes during baseline assessment, 4 weeks, 8 weeks follow-ups, and 3 and 6 months follow-ups after the commencement of the PEMF treatment.

## Methods: participants, interventions, and outcomes

### Study setting {9}

This study will be conducted at the Prince of Wales Hospital in Hong Kong which is the teaching hospital of the Chinese University of Hong Kong. The assessment and intervention will be conducted at the Prince of Wales Hospital Sports Performance and Biomechanics Laboratory.

### Eligibility criteria {10}

Participants will be recruited based on the inclusion and exclusion criteria (Table 1).

**Table 1 Tab1:** Inclusion and exclusion criteria

**Inclusion criteria**
(1) Age between 18 and 70 (2) Focal clinical signs of AT with localised tenderness on palpation of the Achilles tendon (3) Recurrent complaints in 1 or both Achilles’ tendons at rest and during exercise for the preceding 3 months (4) Structural changes of the tendon were confirmed via sonographic examination during the initial physical exam (5) Informed consent
**Exclusion criteria**
(1) History of major injury or surgery on the affected lower limb in the past year (2) Mental/physical limitations hindering participant’s ability to complete assessments including severe cognitive impairment and psychiatric disorders (3) With medical or musculoskeletal problems that could affect the ability to complete assessments and intervention (i.e. pre-existing ankle arthritis, hemiplegia, etc.) (4) With active electronic implants like pacemakers and defibrillators (5) Fractures of the trained body parts within the past 12 months

All of the researchers will obtain written consent from all participants before the commencement of this study. All eligible participants will be informed about this study and given the time they need to consider participation. The investigators of this study will answer all questions from the participants. Participants who are willing to participate should sign an informed consent form. The trial will be conducted in compliance with the Declaration of Helsinki and ICH-GCP. Clinical research ethics approval is obtained from the Joint Chinese University of Hong Kong-New Territories East Cluster Clinical Research Ethics Committee (Reference number: 2021.150).

### Additional consent provisions for collection and use of participant data and biological specimens {26b}

The written consent form consists of the consent provisions for collecting and using participant data. The researcher will keep the information collected for a maximum of 5 years after publication results in PhD thesis and scientific papers. The data collected will be published to the public and in peer-reviewed scientific papers anonymously. This study will not require the use of biological specimens.

In addition to PEMF, all participants will perform eccentric exercise. The first step is stretching exercises for the calf muscles. The stretching is a static stretch of the gastrocnemius (knee in extension) and soleus (knee in flexion). The participants are instructed to hold these for at least 30 s and repeat each exercise three times. There will be a 1-min rest between each stretch. Three sets of 10 repetitions of the eccentric exercises will be carried out once daily for 6 weeks. After 6 weeks, the participants will be instructed to carry out three sets of 10 repetitions three times per week for 6 more weeks. The intensity of the exercise should be such that pain, or discomfort, is experienced in the last set of 10 repetitions. Every session ended with the same static stretch exercise as in step 1. Suppose a participant is unable to complete three sets of 15 repetitions. In that case, the participant is instructed to start with fewer repetitions and sets (a minimum of 2 groups of 10) and progress to the total amount as able [7].

### Criteria for discontinuing or modifying allocated interventions {11b}

The treatment will be stopped, and immediate care will be provided if any significant adverse effects happen during the treatment period, including a substantial increase in the severity of pain or discomfort.

### Strategies to improve adherence to interventions {11c}

Participants may choose the time of sessions that suits them the most during working days. The opening hours of the Sports Performance and Biomechanics Laboratory will be extended to cover the evening hours so that participants may come for assessment after work. A record of compliance to eccentric exercise will be made when they come for PEMF treatment.

### Relevant concomitant care permitted or prohibited during the trial {11d}

There are no restrictions on relevant concomitant care. Participants are allowed to continue with their usual care.

### Provisions for post-trial care {30}

Participants may have access to the research clinic at the Prince of Wales Hospital if they suffer from orthopaedic conditions after the trial.

### Outcomes {12}

#### Patient-reported outcomes

The primary outcome is the score of the Victorian Institute of Sports Assessment-Achilles (VISA-A) questionnaire, which is explicitly designed for Achilles tendinopathy. VISA-A will be used to evaluate pain and symptom severity with activity in participants with AT. Chinese-speaking participants will complete the validated VISA-A HK questionnaire [8]. The VISA-A questionnaire covers three domains associated with AT: pain, function, and sporting activities. A deterioration in self-reported pain, function, and sporting activities is the critical reason patients with AT come for medical consultation. Improving questions covered in VISA-A is often the rehabilitation goal for these patients. Since PEMF was used for pain reduction for other musculoskeletal disorders, similar effects may be applied to patients with AT.

Short Form-36 questionnaires (SF-36) will be used to evaluate health-related quality of life [9]. PEMF may reduce pain levels and allow participants to resume social activities, recreational activities, and functional tasks at work. A numeric pain rating scale (NPRS) will be used to assess the level of pain on the categories “general on the day of review,” “family and responsibility at home,” “recreation,” “social activities,” and “running training or other physical activities.” Each NPRS ranges from “no pain” to “severe pain”.

#### Functional outcomes

##### Ankle range of motion

Weight-bearing lunge test will be used to measure ankle dorsiflexion’s range of motion (ROM). It will be used as an indicator of the flexibility of the gastrocnemius muscle. The participant will maximally dorsiflex the ankle while keeping the knee extended and the heel on the floor [2, 10]. The weight-bearing lunge will be performed in a standing position with the heel in contact with the ground, the knee in line with the second toe, and the great toe. Participants are allowed to place two fingers from each hand on the wall to maintain balance. They will be asked to lunge forward, directing their knees toward the wall until their knees touch the wall. The foot will progress away from the wall, and the subject will repeat the lunge until they cannot touch the wall with their knee without lifting the heel from the ground. A long ruler will be used to measure the distance between the big toe and the wall.

##### Calf muscle strength

The heel-rise test will be used to measure calf muscle strength. The participant will stand on a pressure mat (Tekscan, USA). The information on the plantar pressure will be collected for analysis [11]. Participants will be instructed to keep the knee straight and rise as high as possible on the heel each time until fatigue. They can place two fingertips per hand on the wall to maintain balance. The rhythm will be set at a frequency of 30 heel rises per minute by following a metronome [2]. This study was planned to investigate possible changes in plantar pressure distribution in participants with AT. This study hypothesises that peak pressure, midfoot maximum force, and metatarsal maximum force values in participants with AT during baseline would be lower than that after PEMF treatment. Participants could perform heel rise with better force transmission after improved pain associated with AT after PEMF treatment. Heel maximum force is hypothesised to be higher in participants during baseline assessment than after PEMF treatment. Participants with Achilles tendinopathy may have poorer eccentric control during heel raise. A sudden heel drop from the highest level of heel raise may increase the heel’s maximum force.

#### Ultrasonographic outcomes

The ultrasonographic outcomes are measured by a PhD candidate with 2 years of experience performing ultrasound measurements of the Achilles tendon. A standardised imaging procedure is used to ensure repeatability. Ultrasound examinations for this study will be performed during baseline assessment and all follow‐up visits after inclusion in the RCT. No specific instructions will be provided about activities before the consultation. The participants will be placed in a prone position on the examination table, and the ankle will be placed over the table in a relaxed position. All ultrasounds will be bilateral according to a standardised protocol using the Aixplorer machine (SuperSonic Imagine, Aix-En-Provence, France) equipped with a 12-MHz superficial linear transducer. Participants will be placed in a prone position with their legs extended. The examination will start with grayscale B mode, power Doppler ultrasound, and end with shear wave elastography.

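### Activity before each ultrasound scan is expressly left open while prescribed tendon loading changes from visit to visit, so short-lived loading effects can enter the tendon outcomes

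*Protocol article*

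**What the plan says.** All places are in the protocol article.

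- *Ultrasonographic outcomes*: "A standardised imaging procedure is used to ensure repeatability". Shortly afterwards: "No specific instructions will be provided about activities before the consultation". The order of modalities within the examination is fixed: "The examination will start with grayscale B mode, power Doppler ultrasound, and end with shear wave elastography".
- *Trial design {8}*: outcomes are taken "during baseline assessment, 4 weeks, 8 weeks follow-ups, and 3 and 6 months follow-ups after the commencement of the PEMF treatment". Table 2 puts the ultrasound and the functional tests at the same timepoints.
- *Interventions*: "Three sets of 10 repetitions of the eccentric exercises will be carried out once daily for 6 weeks", then "three sets of 10 repetitions three times per week for 6 more weeks". The programme is the same in both arms, at an intensity that produces pain or discomfort in the last set. Nothing is prescribed after that.
- *Calf muscle strength*: in the heel-rise test participants "rise as high as possible on the heel each time until fatigue".
- *Background and rationale {6a}*: "Patients may experience less pain while performing eccentric exercises to increase compliance with the rehabilitation programme".
- *Objectives {7}*: the second objective includes effects on the mechanical and morphological properties of the tendon.

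**The concern.** The scan measures thickness, Doppler flow and stiffness of a tendon that the trial itself loads. How recently the tendon was loaded is therefore a measurement condition, like position or probe pressure, and it is the one the protocol chooses not to control. Because the protocol states this choice outright, it is not a detail lost in condensing the article.

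Two things could follow if recent loading has a short-lived effect on the readings. First, varying recency of exercise adds scatter to every ultrasound outcome. Because prescribed exercise differs by visit, it also changes systematically along the time axis, so a change from baseline could partly reflect how recently the participant exercised. The Öhberg score is coarse, with adjacent grades that can differ by a single vessel, so a small transient shift could move a grade. Second, if active PEMF makes exercise more tolerable and raises compliance, active participants would more often have exercised shortly before a scan. Randomisation balances characteristics at entry. It does not balance behaviour that the treatment itself changes. A lasting effect on the tendon could then not be told apart from carry-over of recent loading.

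**Working it through.** The plan states no figure to reproduce here. The check sets the exercise schedule against the scan visits.

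**Step 1. Prescribed loading at each scan** (*Interventions*, *Trial design {8}*, Table 2). The programme lasts 6 + 6 = 12 weeks.

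| Scan | Phase of programme | Days with a prescribed session |
|---|---|---|
| Baseline | not yet started | 0% |
| Week 4 | first six weeks | 7/7 = 100% |
| Week 8 | second six weeks | 3/7 = 43% |
| Month 3 | about the end | 43% or 0%, depending on the exact date |
| Month 6 | ended | 0% |

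The baseline row assumes that the first assessment precedes the first exercise session. Table 2 puts both in the Week 1 column.

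**Step 2. How far the arms might differ.** Let g be the difference in exercise compliance between arms. The documents give no value. The difference in the chance of a session on the scan day is

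g × (share of days with a prescribed session).

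| Assumed g | Week 4 | Week 8 |
|---|---|---|
| 0 (equal compliance) | 0 | 0 |
| 0.15 | 0.15 × 100% = 15 points | 0.15 × 43% = 6 points |
| 0.30 (for example 90% v 60%) | 0.30 × 100% = 30 points | 0.30 × 43% = 13 points |

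For same-day sessions these are ceilings at the assumed g, because only a session done before the scan can carry over. They describe exposure and say nothing about the shift in grade, millimetres or kPa.

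**Step 3. What extra noise would cost (illustration only).** The plan gives no effect size for ultrasound outcomes. Borrow the VISA-A figures from *Sample size {14}*: d = 16/20.25 = 0.79, with 20 per arm. Suppose uncontrolled activity adds a share s to the outcome variance. By normal approximation at two-sided 5%,

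power = Φ( d/√(1+s) × √(20/2) − 1.96 ).

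| s | d/√(1+s) | Power |
|---|---|---|
| 0 | 0.79 | 70% |
| 0.10 | 0.75 | 66% |
| 0.25 | 0.71 | 61% |
| 0.50 | 0.65 | 53% |
| 1.00 | 0.56 | 42% |

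Both d and s are assumptions. The table shows only how sensitive a simple two-group comparison of this size would be to added variance. It is not a check of the planned sample size, which is for VISA-A with a repeated-measures analysis.

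**Step 4. The heel-rise test.** It shares timepoints with the scan. The article fixes the order within the ultrasound examination, but not the order of the scan and the functional tests, nor any rest between them. The test can affect the reading only if it comes first.

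**The case against.** The strongest reply is that no harm is shown. Nothing in the documents says that recent loading alters thickness, Doppler flow or stiffness, so the whole concern rests on that premise. This stands, and it is why the point is worded as what can happen.

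A reader might infer that the ultrasound comparison between arms is biased. The documents do not support that. Both arms have the same exercise programme and the same visits, so the schedule alone does not favour either arm. Bias would need three further things: that PEMF does raise compliance (the rationale says only that it may), that the extra sessions fall shortly before scans, and that the acute effect is material. A reader might also infer that the heel-rise test contaminates the scan. The order is unstated, and the article does not say that the test is done on one leg. Test order is also a detail that an article may leave to the full protocol, and the point does not depend on it.

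It can further be said that the standardised procedure refers to image acquisition, so the two sentences do not strictly contradict each other. That is fair. Acquisition controls exist: a relaxed prone position, a one-minute Doppler preparation phase, and elastography signals held steady for five seconds. None of them controls loading before the visit. Exercise compliance is recorded at PEMF visits (*Strategies to improve adherence {11c}*), which helps up to week 8. It is not described as time since last exercise at a scan, and PEMF visits end before the month 3 and month 6 scans.

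Finally, enrolment began on 1 July 2021 (*Trial status*), so a change would make earlier and later scans differ in preparation. That is a real cost, and the fix allows for it.

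**Conclusion.** The point holds in a limited form. The protocol expressly leaves recent tendon loading uncontrolled at the scan, while its own exercise programme moves from none to daily, to three times a week, to its end and to none across the five assessments. If recent loading has a short-lived effect, it adds noise to the ultrasound outcomes and clouds their change from baseline in both arms. Bias between arms is possible if compliance differs, but it is not demonstrated.

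No shift in any outcome can be calculated from the documents. The compliance gaps and variance shares above are assumptions. The consequence is confined to thickness, neovascularity and stiffness, which are secondary but belong to a stated objective. VISA-A and its sample size are untouched.

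**What to change.** Replace the sentence on activity before the consultation with a standard measurement condition for all five assessments:

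1. Do the ultrasound after a short fixed rest and before the lunge test, the heel-rise test and any PEMF or sham session that day.
2. At each scan, record the time since the last eccentric exercise and the last sport.
3. Report that time by arm and visit. It may itself be affected by treatment, so use it to describe balance and interpret the results, and do not adjust for it in the main comparison.

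Leave the exercise prescription unchanged. The cost is one extra case report form field and a fixed order for tests already planned, with no added procedure or staff. Scans already made under the present rule should be flagged in the dataset, so that the two preparation conditions can be told apart.
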